#### Primary outcome measure

##### The Knee injury and osteoarthritis outcome score (KOOS-ADL)

KOOS is patient-reported outcome measure with good evidence of reliability, validity and responsiveness in different population with varying pathologies, injury durations and activity levels
[35-37]. A 5-point Likert-scale is used and converted into a 100-point scale with zero indicating the worst possible health
[35].

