### Statistical analysis

The primary statistical analysis will be performed on KOOS-ADL 3-month following surgery. To evaluate the treatment effect (mean difference in KOOS scores) we will employ a random or fixed effects linear regression model with point estimates
[62] and both crude and adjusted results will be reported. The regression model includes the interaction between treatment and elapsed time, adjusted for pre-surgery values and assumes data is missing completely at random (MCAR)
[62]. Model assumptions will be checked by residual plots. The secondary statistical analysis will include the same approach as described above for all the secondary outcomes. All analyses will be performed on the basis of intention-to-treat (ITT)
[63]. However, subsequent per-protocol analysis may be necessary in the event of a substantial number of patients (> 15%) being lost during follow-up. All data will be checked for Gaussian distribution and parametric statistics will be used were appropriate, otherwise non-parametric statistics will be applied. Finally, the number needed to treat (NNT) for a positive effect of treatment (>10 points on KOOS-ADL) will be analyzed. All statistical analyses are blinded and will be performed using Stata software (StataCorp, Texas, USA).

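### The Gaussian rule for all data does not exempt KOOS-ADL, so it could move the primary analysis off its named baseline-adjusted model and change what is estimated

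*Protocol article*

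**What the plan says.** All of this stands in one paragraph of the protocol article, Statistical analysis.

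- Outcome and time point: "The primary statistical analysis will be performed on KOOS-ADL 3-month following surgery".
- Estimand and model: "To evaluate the treatment effect (mean difference in KOOS scores) we will employ a random or fixed effects linear regression model with point estimates".
- Terms in the model: "The regression model includes the interaction between treatment and elapsed time, adjusted for pre-surgery values".
- Check on the model: "Model assumptions will be checked by residual plots". No consequence of a poor plot is stated.
- Reach: "The secondary statistical analysis will include the same approach as described above for all the secondary outcomes".
- Distribution rule, further down: "All data will be checked for Gaussian distribution and parametric statistics will be used were appropriate, otherwise non-parametric statistics will be applied". It gives no test, no threshold, no scale (raw score, change or residual) and no replacement method.
- Blinding: "All statistical analyses are blinded and will be performed using Stata software".

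The section on the primary outcome measure describes the scale: "A 5-point Likert-scale is used and converted into a 100-point scale with zero indicating the worst possible health". The Sample size section sets a 10-point target with SDs of 18.5 before and 10.4 after surgery, and arrives at 36 per group, or 40 with drop-outs.

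**The concern.** The paragraph holds two checks on the primary analysis. The residual plots suit a linear model but lead to no stated action. The Gaussian check on the data suits it less well, yet it is the one that decides the method. A linear model does not need Gaussian raw scores. It needs roughly normal residuals, or enough patients for the mean difference to be approximately normal.

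What is at stake is the estimand. The trial is sized on 10 KOOS-ADL points. A standard rank test answers a different question: it gives no mean difference in points, takes no account of the pre-surgery score and has no treatment-by-time term. Whether the primary result is on the planned scale would then be settled only after the outcome data are in. The same applies to the continuous secondary outcomes, which follow the same approach.

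**Working it through.** **1. The plan's own figure.** Inputs from Sample size: difference 10, SDs 18.5 and 10.4, α = 0.05 (taken as two-sided), and the stated β of 0.80 read as power. With two unequal SDs,

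n per group = (z₀.₉₇₅ + z₀.₈₀)² × (SD₁² + SD₂²) / δ² = 7.849 × (342.25 + 108.16) / 100 = 35.35, rounded up to 36.

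The figure of 36 is reproduced, and it is a calculation for a difference in means. The target and the sizing are therefore both on the points scale, which a rank test does not report.

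**2. The two statements compared.**

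| | Named model | Gaussian rule |
|---|---|---|
| Applies to | KOOS-ADL at 3 months, and the secondary outcomes | all data |
| What is checked | residuals | distribution of the data |
| Stated consequence | none | choice of method |
| What is estimated | mean difference in points, baseline-adjusted | depends on an unnamed method |

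Nothing says which statement governs when they disagree.

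**3. How often might the rule fire?** The article gives no 3-month mean, no distribution shape and no ceiling rate, so these are assumptions. KOOS-ADL has 17 items with five options each (Discussion), so scores move in steps of 100/68. Simulated scores were taken from a normal clipped at 0 and 100, or from a scaled beta, with 38 per arm (between 36 and 40). Shapiro-Wilk was applied at 5% to the pooled within-arm residuals. The cells show the rejection rate, clipped normal to beta.

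| Assumed mean | SD 10.4 | SD 18.5 |
|---|---|---|
| 55 | 5% to 6% | 3% to 12% |
| 70 | 4% to 23% | 19% to 84% |
| 75 | 5% to 42% | 57% to 99% |
| 80 | 7% to 75% | 92% to 100% |
| 85 | 44% to 99% | about 100% |
| 90 | 98% to 100% | 99% to 100% |

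The range is about 3% to 100%, and the test itself is an assumption.

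**4. Does a switch cost power?** Assumptions: 36 per arm, true difference 10, correlation 0.5 and pre-surgery mean 50.

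With little skew (3-month mean about 75):

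| SD at 3 months | ANCOVA | Mann-Whitney, 3-month score | Mann-Whitney, change score |
|---|---|---|---|
| 10.4 | 99.7% | 97.9% | 69% |
| 18.5 | 72% | 60% | 52% |

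With skewed, bounded scores (scaled beta on the 17-item grid, 2,000 replicates), where a normality check is more likely to fire:

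| SD, arm means | ANCOVA | Mann-Whitney, 3-month score |
|---|---|---|
| 10.4, 75/85 | 99.7% | 98.8% |
| 10.4, 80/90 | 99.0% | 99.6% |
| 15, 70/80 | 87% | 84% |
| 15, 75/85 | 86% | 90% |
| 18.5, 70/80 | 72% | 73% |
| 18.5, 75/85 | 71% | 85% |

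Under marked skew the rank test on the 3-month score is close to ANCOVA or ahead of it. A rank test on change scores does lose power in the first table, but the article does not name that test.

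**5. Type I error.** Under no difference, each single test rejected in 4.3% to 5.8% of simulated trials. The two-stage procedure (Shapiro-Wilk first, then ANCOVA or Mann-Whitney) rejected in about 5%.

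**The case against.** The strongest reply is that the paragraph first commits to the linear model without condition and gives it its own check. The later sentence would then be a general convention for data outside that model, such as surgical data, medication quantities or biopsy measures. This reading is possible, but the sentence covers all data and makes no exception for KOOS-ADL, so the text does not secure it.

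A second reply is that the fallback is unnamed and its detail may belong to the analysis plan. A rank-based or bootstrap method could keep the baseline adjustment. That is fair, and it makes the change of estimand conditional. The point, however, is a rule the article does state, not detail that it leaves out.

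A third is that the analyses are blinded. That limits selective choice of method. It does not stop the method from depending on the data, and it does not fix the estimand.

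A reader might also infer three stronger things that the document does not support:

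- *That the switch is probable.* The bounded scale and the fall in SD from 18.5 to 10.4 are compatible with a ceiling but do not show one. No mean, shape, test or threshold is given, and the wording leaves room for judgement.
- *That a switch would lose power.* This is not so in general. The clear losses for a rank test on the 3-month score appear with near-normal scores and a large SD, not under the marked skew that would trigger the rule.
- *That pre-testing inflates type I error.* The simulations show no inflation.

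**Conclusion.** The point holds in a conditional form. As written, the Gaussian rule reaches the primary outcome, is not reconciled with the named model, and rests on the distribution of the data where the model's assumption concerns the residuals. If it fires and a standard rank test follows, the trial loses the mean difference in points, the baseline adjustment and the repeated measures, and its result cannot be read directly against the 10-point target.

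The probability of this is undetermined: about 3% to 100% under an assumed 5% Shapiro-Wilk test with assumed means, SDs and shapes. The case therefore rests on fixing the primary method and its estimand in advance, not on power or error rates. It should be corrected, because the rule is stated in the protocol and the correction is nearly free.

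**What to change.** Add one sentence to Statistical analysis: the Gaussian rule does not govern KOOS-ADL or the continuous secondary outcomes analysed with the same model. For these:

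- keep the baseline-adjusted linear model with the treatment-by-time interaction, whatever the distribution of the raw scores;
- if the residual plots show marked skew, use robust or bootstrap standard errors for the same mean difference;
- report any rank-based analysis as a named sensitivity analysis only.

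The rule can stay for data outside the model. The cost is one sentence and a small amount of extra analysis. The sample size stays at 36 per group, 40 with drop-outs.

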### Sample size

Sample size estimation was performed upon the primary outcome KOOS-ADL, using one pre-surgery and 2 follow-up assessments and an estimated correlation between follow-up measurements of 0.5. Based upon data from a non-randomized, but controlled study from Sweden, a 10-point change in KOOS-ADL (SD of 18.5 pre-surgery and 10.4 post-surgery) has been selected as clinical important difference at the 3-months end-point. A sample size of n = 36 is needed in each group (α = 0.05, β = 0.80)). To account for possible drop-outs n = 40 will be included in each group.

### Timeline and ethics

Recruitment of patients is scheduled to begin in spring 2014 and will last for 1 year. All patients are expected to have completed the trial by spring 2016. The omission of tourniquet use is expected to only marginally increase surgery time (~ 5 min.), and the increased surgery time is unlikely to increase the risk of complications. In contrast, total theatre time is expected to remain unchanged due to the time saved when application of the tourniquet is omitted. No difference, or a slight non-critical increase, in total blood loss in the non-tourniquet group is expected
[15]. The trial complies with the Declaration of Helsinki and the trial has been approved by the Regional Ethics Committee of Southern Denmark (S-20110084).

## Discussion

This clinical trial will evaluate the efficacy of tourniquet assisted TKA on patient-reported and performance-based physical performance As a prospective randomized controlled trial the results of this study will provide a high level of evidence on the clinical implications of using a tourniquet during TKA. The primary end point, at 3-month, is a sufficiently long timeframe for the relevant clinical improvements between groups to show and yet short enough to assume that patients can recall their baseline condition. As part of the design, a single senior surgeon will perform the surgical procedures in both groups. The experience of the surgeon in both tourniquet-assisted and non-tourniquet TKA and use of random block size randomization will eliminate bias due to learning. Additionally use of a single surgeon will ensure we are comparing the TKA procedure rather than the skill of different surgeons.

The key aim of TKA in patients with OA is to relieve pain and improve function, both of which are patient reported outcome (PROs) measures reflected in the design of this trial and recommended outcome measures by the Osteoarthritis Research Society International (OARSI) and Outcome Measures in Rheumatology and Clinical Trials (OMERACT) group
[39]. Ideally, changes in physical function following TKA should be evaluated using a combination of patient-reported outcomes (PROs) and performance-based outcome measures
[39,45] as they are complementary rather than competing
[64,65] and capture different constructs of physical function
[66,67]. In addition, responsiveness of a PROs ability to detect when patients are undergoing relevant clinical changes can be assessed using a global response evaluation (GPE), and a GPE questionnaire is a recommended part of the evaluation of a treatment in clinical trials
[38,39]. To accommodate these recommendations, the patients in the present trial will be asked to rate their current knee condition pre-surgery (baseline), and at each follow-up (KOOS) and also rate changes in their condition since baseline (GPE). These two patient-reported outcome measures (KOOS and GPE) will be supported by assessor-observed performance-based tests of physical function, hence evaluating, what ‘patients can do’ rather than what they ‘perceive they can do’
[67].

According to WHOs classification of Functioning, Disability and Health (ICF) physical function can be classified as the ability to “perform daily activities”
[68]. Hence, to fully capture physical function in patients following joint replacement, performance-based testing should represent a variety of physical function domains (activity themes) representing the following five daily activities; *walking, sit-to-stand, ambulatory transitions, stair negotiation, and endurance*[45]. The current trial uses the 2×20 m fast-paced walk test, the 30-s chair-stand test, and the timed up-and-go test evaluate; walking, sit-to-stand, and ambulatory transition activity domains, repetitively. Despite the importance of also evaluating *stair negotiation activity,* no specific test is planned in the trial for two reasons. First, no recommendations about specific performance-based tests of physical function, with good measurement-property evidence (reliability, validity, responsiveness, and interpretability), is currently available. Second, the feasibility of stair negotiation tests is largely dependent on the environmental setting making them unsuitable for clinical trials at present
[45]. Likewise, no test for evaluating *endurance activity* has been planned for this trial due to the practical feasibilities issues associated with the six-minute walk test, e.g. patients are unable to walk for six minutes and exhausted following surgery. Further, endurance activity evaluation may be compromised in the early post-surgery phase since pain and swelling, rather than endurance, could limit patients’ performance. Consequently the current trial evaluates three primary activity themes using a core set of performance-based tests recommended by OARSI
[45], and from this core set of tests efficient comparisons of treatment outcomes across published literature can be made.

Evaluating the domain of pain or physical function in patients following joint replacement surgery is important
[39]. However, the decision to nominate physical function as primary outcome was due to two reasons. The KOOS questionnaire evaluates physical function in a variety of daily activities, and has an extensive subscale (KOOS-ADL, 17 items) devoted to evaluate physical function compared to the pain-subscale (KOOS-PS, 10 items). Additionally, WOMAC and KOOS are the most common PROs used to capture patient relevant information, relating to the impact of interventions in clinical research
[69]. WOMAC scores can subsequently be calculated based on data collected using the KOOS questionnaire, thus making efficient comparisons across published literature possible.

Essential explorative outcome measures are also included in the present trial to study muscle mechanics and potential microscopic muscle damage. Studying muscle mechanics is clinical relevant in understanding body structure
[51,70] and the recovery of muscle strength and power are likely to be compromised in tourniquet assisted TKA patients. The theoretical disadvantages of tourniquet application on muscle mechanics is supported by one randomized trial
[7] and two non-controlled studies in which reduced muscle function and neurological impairment have been reported
[29,71]. However, such findings should be confirmed in high-quality trials using randomized designs.

A number of other factors may also influence the effects of tourniquets
[15]. It’s been suggested that the tourniquet position may be of clinical importance
[72] but also cuff width, cuff pressure, time of cuff deflation (cementation of the prosthesis, would closure or application of dressing) must be considered factors that may affect outcome, and should be recorded
[15]. Other factors include use of thromboprophylaxis, girth/circumference of thigh, and patient blood pressure. Data on these variables will be collected to insure uniform presentation of data in peer-reviewed papers
[9,15].

## Conclusion

We have designed a randomized clinical trial with the main purpose of investigating the efficacy of tourniquet assisted TKA on patient-reported physical function, an outcome which will be supported by a range of performance-based secondary outcome measures. This part of the trial will provide results with high-level evidence and may help to determine whether tourniquet should be used in future TKA procedures for those with severe osteoarthritis of the knee. The explorative part of the trial could also provide further understanding of the underlying neurological and muscle mechanical impairments associated with use of tourniquet during TKA surgery. The results will be submitted to a peer-reviewed international journal for publication irrespective of the outcome in accordance with the CONSORT guidelines for reporting of clinical trials.

## Abbreviations

ADL: Activities of daily living; GPE: Global perceived effect; KOOS: The knee disability and osteoarthritis outcome score; iMVC: Isometric maximal voluntary contraction; QoL: Quality of life; TKA: Total knee arthroplasty; VAS: Visual analog scale; LEP: Leg extension power.
